#### Implementation {16c}

Assignment to the intervention or control arm will be undertaken by the randomisation team at the National Health and Medical Research Council Clinical Trials Centre (NHMRC CTC). A customised randomisation system has been created for SWIFT. Clusters are sorted by stratification factors, paired, then arm allocation within pairs is determined by random selection (using the current date as a seed).

### Assignment of interventions: blinding

#### Who will be blinded {17a}

Blinding to allocation is not possible within clusters due to the nature of the intervention; however, all staff compiling and analysing outcome data will be blinded to allocation.

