#### Intervention description {11a}

The intervention comprises regular measurement of symptom burden with feedback of these results to participants and clinicians. Participants in the intervention arm will complete the IPOS-Renal at baseline, 3 months, 6 months, 9 months and 12 months, within a 2-week window (Table 1). The individual participant’s IPOS-Renal results will be emailed to the centre nurse unit manager or delegate, and the participant’s treating nephrologist. Within the email will be a link to evidence-based guidelines for symptom management. The evidence-based guidelines were created by SWIFT Investigators (RLM and AKV) and are updated regularly (SWIFT Investigator BS) to ensure new evidence is incorporated. Any symptom score of 3 (severe symptoms) or 4 (overwhelming symptoms) on a scale of 0–4, on the IPOS-Renal instrument will be flagged for prompting clinical review. All subsequent medical treatments are at the discretion of the treating clinicians. Participants receive a copy of the completed survey emailed to them in real-time if they provide an email address at commencement of the survey. Based on our previous work, we anticipate about 30–40% of participants will provide an email address [17]. If a participant does not have their own email address, they can nominate the address of a family member or close friend. Participants do not receive the evidence-based guidelines for symptom management.

**Table 1 Tab1:** Study timeline schedule

	Patient screening	Baseline	3 months	6 months	9 months	12 months
Patient demographics	X					
Informed consent		X				
EQ-5D-5L questionnaire		X		X		X
SONG-HD Fatigue questionnaire		X		X		X
IPOS Renal (*intervention arm only*)		X	X	X	X	X
Validity questions (all participants)		X		X		X
ANZDATA clinical treatment record	X	X	X	X	X	X
MBS and PBS data						X

*Abbreviations: EQ-5D-5L*, EuroQoL 5-item 5-level preference-based measure of health status, *IPOS Renal*, Integrated Palliative Outcome Scale – Renal, *SONG-HD Fatigue*, Standardised Outcomes in Nephrology – Haemodialysis, Fatigue

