#### Concealment mechanism {16b}

Once participating sites are confirmed, the allocation process will be undertaken by the trial statistician (CB) and kept concealed until the site initiation visit. Access to the allocations is limited to the CI (RLM), the trial statistician (CB), the CTC trial operations coordinator (PW) and ANZDATA Registry Manager ([name]) to minimise risk of inadvertently influencing sites or prematurely revealing allocation.

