### Data collection and management

#### Plans for assessment and collection of outcomes {18a}

Data is collected electronically via an Android tablet (five timepoints for the intervention arm and three timepoints for the control arm) and stored in the Qualtrics survey platform (Qualtrics, Utah, 2021). Each individual participant has a unique quick response (QR) code assigned to them for the duration of the trial that matches a unique “SWIFT ID”. Participant responses are automatically downloaded from the Qualtrics survey platform every 15 min (see data management statement below). The response date is automatically marked off for all survey responses. A manual query is run by LMG daily to determine if there is a duplicate response or if the incorrect QR code is scanned for a participant so the response can be queried with the centre. ANZDATA also receives a notification via email with the participant’s SWIFT ID, date of survey completion and the survey response for each participant as an additional check.

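### The blanket blinding claim for outcome staff is wrong for those who compile the data, and is not secured for the primary analysis

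*Protocol article*

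**What the plan says.** All places are in the protocol article.

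- Who will be blinded {17a} accepts that blinding within clusters is impossible, then states without exception that "all staff compiling and analysing outcome data will be blinded to allocation".
- Concealment mechanism {16b} says that "the allocation process will be undertaken by the trial statistician". It opens the access list with "Access to the allocations is limited to the CI" and closes it with "and ANZDATA Registry Manager". The trial statistician and the trial operations coordinator stand between them, which makes four roles.
- Implementation {16c} says: "Assignment to the intervention or control arm will be undertaken by the randomisation team", at the coordinating clinical trials centre.
- Plans for assessment and collection of outcomes {18a} gives the survey schedule as "five timepoints for the intervention arm and three timepoints for the control arm". The registry is also notified by email of each participant's trial ID, "date of survey completion and the survey response for each participant as an additional check".
- Intervention description {11a}: "Participants in the intervention arm will complete the IPOS-Renal at baseline, 3 months, 6 months, 9 months and 12 months". Explanation for the choice of comparators {6b} says that the control arm does not complete this electronic measure, and Table 2 defines symptom severity for the intervention arm alone.

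**The concern.** Participants and clinicians know the allocation and the primary outcome is self-reported, so the statement in {17a} is the only masking that the trial claims. The data flow described elsewhere in the same article does not have that property for the people who compile the data. It may not have it for the primary analysis either, depending on who runs it. If the sentence is carried into the trial report, readers will credit a safeguard against arm-aware data handling and analysis decisions that the described design does not provide. This is not a complaint about detail left to the SAP: {17a} is a positive statement, and other sections conflict with it.

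**Working it through.** The plan attaches no figure to blinding, and nothing in the sample size depends on it. The check is a comparison of statements.

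**1. Who handles the outcome data.** Under Data management, survey data pass daily from the survey platform to the trial's module in the registry and stay there until analysis. Under {18a} the registry also receives the individual response by email, and a manual query for duplicate or wrongly scanned responses is run daily. The article does not say that the same staff do both. The argument does not need that: receiving the response is enough.

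**2. What a record shows** (Table 1, {6b}, {11a}, {18a}).

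| Record | Intervention | Control |
|---|---|---|
| EQ-5D-5L, SONG-HD Fatigue | baseline, 6, 12 months | baseline, 6, 12 months |
| IPOS-Renal | baseline, 3, 6, 9, 12 months | none |
| Survey timepoints | 5 | 3 |

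The difference, 5 − 3 = 2, is the 3- and 9-month surveys. At the three shared timepoints the intervention record also carries IPOS-Renal. So all five intervention timepoints reveal the arm, starting at baseline.

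**3. Reach of one record.** Trial design {8} randomises centres and forces linked centres to the same arm. One IPOS-Renal record therefore reveals the arm of every participant in that cluster.

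**4. Against {17a}, compiling.** Staff who receive or compile these records can see the arm. The claim fails for them without any inference from job titles.

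**5. Against {17a}, analysing.** Two cases differ.

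- Analyses that use IPOS-Renal cannot be blind. Symptom severity exists in one arm only, and Methods for additional analyses {20b} plans to relate symptoms to EQ-5D-5L within the intervention group.
- The primary analysis uses EQ-5D-5L, collected at the same three times in both arms. An extract limited to it and to registry fields, with masked arm codes, has the same structure in both arms and can be analysed blind by someone who does not hold the allocations.

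**6. The holders of the allocations.** Two of the four roles in {16b}, the trial statistician and the registry manager, could belong to the group that {17a} calls blinded. That needs an assumption for each: that the statistician runs the outcome analysis, and that the manager personally compiles data. The article states neither and excludes neither. If the statistician runs the primary analysis, a dummy code does not restore blinding, because that person already knows the arms.

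**7. Who allocates.** {16b} names the trial statistician and {16c} a randomisation team. The two agree if the statistician belongs to that team, but the article does not say so.

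**The case against.** The strongest reply is that only the word *all* is too broad. Responses are entered by participants on a tablet and downloaded automatically, so no staff member rates the outcome. The primary model and its adjustment are stated, the sensitivity exclusions are named in advance, and missing-data detail is properly deferred to the SAP. The manual query covers duplicates and wrong codes and is settled with the centre. A separate blinded analyst may be named in a document not shown. The access list in {16b} serves concealment until site initiation and does not describe who is blind at analysis.

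Most of this stands, and it limits the likely harm. It does not rescue the statement about compiling staff.

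Three stronger readings are tempting but unsupported:

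- *That the trial has no blinding at all.* The primary EQ-5D-5L data can still be analysed blind, as step 5 shows.
- *That the statistician and the registry manager are shown to breach the claim.* No section says that either one analyses or personally compiles outcomes.
- *That {16b} and {16c} contradict each other.* They are compatible if the statistician is part of the team.

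**Conclusion.** The statement in {17a} is wrong as written. Staff who compile the surveys can identify the arm from any intervention record and, through the cluster, the arm of the whole centre. That conclusion rests on the text alone.

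The second part is conditional: the primary analysis is also unblinded if the statistician who allocates runs it, which the article leaves open.

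The size of any bias cannot be computed from the document, and nothing here shows that bias will occur. The point merits correction because it concerns the only masking claimed, and because a blinded primary analysis is still within reach.

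**What to change.** 1. Reword {17a} so that the claim covers the primary analysis only. State that registry data-handling staff, and everyone with access to the allocations, are not blinded.
2. Run the primary analysis on an extract of baseline, 6- and 12-month EQ-5D-5L and registry fields, without IPOS-Renal or 3- and 9-month records, and with arm under a dummy code.
3. Have it run by an analyst without access to the allocations where one is available. Otherwise report the primary analysis as not blinded.
4. Finalise the SAP and the primary analysis code before the key is released.
5. Align {16b} and {16c} on who allocates.

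Moving the allocation list to another team would not be enough. Randomisation proceeds state by state as centres agree, and recruitment opened on 7 April 2021, before the article appeared on 19 May 2022. Allocations already made cannot be unlearned.

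The cost is revised wording, a restricted extract and a short delay before unmasking, plus a second analyst's time where one is used. Sample size, visits and participant burden do not change.

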#### Procedure for unblinding if needed {17b}

Not applicable as intervention blinding is not possible.

### Data collection and management

#### Plans for assessment and collection of outcomes {18a}

Data is collected electronically via an Android tablet (five timepoints for the intervention arm and three timepoints for the control arm) and stored in the Qualtrics survey platform (Qualtrics, Utah, 2021). Each individual participant has a unique quick response (QR) code assigned to them for the duration of the trial that matches a unique “SWIFT ID”. Participant responses are automatically downloaded from the Qualtrics survey platform every 15 min (see data management statement below). The response date is automatically marked off for all survey responses. A manual query is run by LMG daily to determine if there is a duplicate response or if the incorrect QR code is scanned for a participant so the response can be queried with the centre. ANZDATA also receives a notification via email with the participant’s SWIFT ID, date of survey completion and the survey response for each participant as an additional check.

#### Plans to promote participant retention and complete follow-up {18b}

The SWIFT Pilot Study [17] determined that an important facilitator to the uptake and engagement in the trial was a nurse champion in each centre. These nurse champions influenced the rates of recruitment within each haemodialysis centre. Participant retention is potentially high given that the participants are attending their haemodialysis centre three times per week, unless they receive a transplant, die, stop haemodialysis or are transferred to another non-participating haemodialysis centre. Additionally, consumer involvement in the design of the trial was to aid feasibility. Symptoms are 3 of the top ten patient research priorities [28]. Dialysis patients and their family members have helped select the most meaningful and feasible QOL instruments.

#### Data management {6}

The data is stored in the Qualtrics (Qualtrics, Utah, 2021) survey platform and then securely transferred daily to the SWIFT module within the ANZDATA Registry. Data is transferred through use of an application programming interface (API) developed between ANZDATA and Qualtrics. Data will be stored in tables within the SWIFT ANZDATA module until analysis.

#### Confidentiality {27}

All data generated in this trial will remain confidential. All information will be stored securely at the NHMRC CTC, University of Sydney and ANZDATA (located within the South Australian Health and Medical Research Institute [SAHMRI]) and will only be available to trial investigators undertaking data cleaning and analysis. Personal data identifying trial participants will be held securely at the NHMRC CTC and ANZDATA for the purpose of data matching with the Health Insurance Commission (HIC). HIC approvals will be obtained.

#### Plans for collection, laboratory evaluation and storage of biological specimens for genetic or molecular analysis in this trial/future use {33}

Not applicable, no biological samples will be collected.

### Statistical methods

#### Statistical methods for primary and secondary outcomes {20a}

The primary analysis will compare symptom monitoring with feedback versus usual care to evaluate the effect of this intervention on QOL and secondary outcomes at 12 months. Change in EQ-5D-5L (from baseline) will be evaluated at 12 months using a generalised estimation equation regression model, adjusted for stratification factors and accounting for clustering. Analysis of outcomes will be compared using an intention-to-treat analysis and individual participant data will be used for all analyses. Sensitivity analyses excluding clusters that currently use IPOS-Renal as a part of their usual care and excluding participants actively managed through a kidney supportive care programme will be undertaken.

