***Primary outcome***		
Health-related quality of life	Mean change in EQ-5D-5L value (utility) from baseline to 12 months (primary outcome)	Baseline, 6 months, 12 months

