### Sample size {14}

SWIFT will recruit 143 haemodialysis centres (or clusters) in Australia. Recruitment data from the SWIFT pilot study confirmed the assumptions of over 50% patient participation in each centre, and 80% completion of EQ-5D-5L at 12 months [17]. Sites are grouped into clusters (see 16a) of approximately 2 sites/cluster. Approximately seventy-one clusters in each arm (equating to 2422 total participants) will enable us to identify a clinically significant mean (0.07) 7% increase in health-related quality of life (from 0.59 [59%] to 0.66 [66%]) with 90% power. This minimum clinically important difference was determined through review of EQ-5D-5L studies that showed a change in overall utility of between 0.03 and 0.07 across a range of chronic conditions was associated with meaningful and observable improvements in QOL. This minimum effect of 0.07 was considered feasible and is supported by an observational study in New South Wales (NSW) that demonstrated improvement in EQ-5D-5L utility of 0.11 could be achieved with a focus on symptom management (internal publication). The power calculation is based on a two-sided *t*-test with alpha=0.05 and assumes a modest intra-cluster correlation coefficient of 0.1 and a design effect of 3.5 (to account for clustering, allowing for uneven cluster sizes) creating an effective sample size of 692. We assume a standard deviation (SD) of the change between baseline and 12 months of 0.281. The 7% represents a conservative estimate in effect however one which demonstrates a clinically meaningful improvement in QOL and translates to a societal benefit of 640 quality-adjusted life years (QALYs) per year.

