### Assignment of interventions: allocation

#### Sequence generation {16a}

ANZDATA centres (i.e. clusters) will be randomised to intervention or control. The randomisation takes place, on a state-by-state basis using the method of minimisation as they agree to participate. This occurs once the SWIFT team has received the feasibility forms for all eligible centres in a state and confirmed which sites will participate. Centres (clusters) may consist of more than one site if frequent patient movement or otherwise close institutional linkages between sites prohibit distinction into multiple functionally distinct clusters. The randomisation will be stratified based upon location (state), metropolitan or regional, private or public unit or prior or current use of the IPOS-Renal questionnaire for symptom monitoring within each centre and cluster size. This will diminish potential confounding by these factors.

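### The primary GEE on change in EQ-5D-5L does not name baseline EQ-5D-5L as a covariate; adding it is free and raises power.

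*Protocol article*

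**What the plan says.** Table 2 of the protocol article defines the primary outcome as "Mean change in EQ-5D-5L value (utility) from baseline to 12 months (primary outcome"). Section {20a} analyses that change "using a generalised estimation equation regression model, adjusted for stratification factors and accounting for clustering". The factors are in section {16a}: "The randomisation will be stratified based upon location (state), metropolitan or regional, private or public unit or prior or current use of the IPOS-Renal questionnaire", with cluster size added at the end of the same sentence. All of them describe centres. None is the participant's own baseline utility.

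Section {14} powers the trial on the same scale: "We assume a standard deviation (SD) of the change between baseline and 12 months of 0.281". The calculation takes a t-test at the two-sided 5% level with an ICC of 0.1, and inflates for clustering through "a design effect of 3.5 (to account for clustering, allowing for uneven cluster sizes) creating an effective sample size of 692". It claims no gain from adjusting for baseline.

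Table 1 and the text of section {12} show EQ-5D-5L collected at baseline, 6 and 12 months in both arms. Section {20c} refers to a statistical analysis plan for further detail, in the context of missing data.

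**The concern.** A raw change score fixes the coefficient of the baseline value at 1. When the baseline to 12-month correlation is below 1 and the SDs are similar, the best-fitting coefficient is smaller, so the change score subtracts too much of the baseline. Two things follow. The treatment effect is estimated with more noise than necessary. And if the arms happen to differ in baseline EQ-5D-5L, part of that difference enters the estimated effect through regression to the mean.

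The precision matters here because the stated total appears to have no slack. 692 × 3.5 is exactly 2422, so if 2422 is the number recruited there is no visible allowance for the 80% completion that section {14} itself expects.

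**Working it through.** **Inputs from the article (section {14}).** Difference 0.07; SD of change 0.281; two-sided alpha 0.05; power 90%; design effect 3.5; effective sample size 692; total 2422; 12-month completion 80%. Allocation is 1:1 (section {8}).

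**Assumptions not in the article.** Correlation rho between baseline and 12-month EQ-5D-5L, varied from 0.3 to 0.8; equal SDs at the two times; design effect unchanged at 3.5 after adjustment.

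**Step 1: reproduce the plan.** The normal approximation gives 339 per arm, 678 in total (680 by t-test), for 90% power. The stated 692 is within 3% of this. With 346 per arm the standard error is 0.281 × √(2/346) = 0.0214, and power is Φ(0.07/0.0214 − 1.96) = 90.6% (90.5% by t-test). 692 × 3.5 = 2422. The plan's figures hold.

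**Step 2: variance ratio.** With common SD s:
- change score: Var = 2s²(1 − rho)
- baseline-adjusted: residual Var = s²(1 − rho²)
- ratio = (1 + rho)/2

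The residual SD is therefore 0.281 × √((1 + rho)/2).

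**Step 3: power, unadjusted against adjusted.** The last column takes 2422 as the number recruited with 80% completing: 0.8 × 2422/3.5 = 554 effective.

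| rho | variance ratio | residual SD | power at 692 | power at 554 |
|---|---|---|---|---|
| unadjusted | 1 | 0.281 | 90.6% | 83.4% |
| 0.3 | 0.65 | 0.227 | 98.2% | 95.3% |
| 0.5 | 0.75 | 0.243 | 96.6% | 92.3% |
| 0.7 | 0.85 | 0.259 | 94.5% | 88.9% |
| 0.8 | 0.90 | 0.267 | 93.2% | 87.1% |

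At rho 0.6 the ratio is 0.80 and 554/0.80 = 692. The loss from non-completion is thus fully recovered for rho up to about 0.6, and only partly above that. If the design effect is recomputed for the smaller clusters, the unadjusted figure at 80% completion is about 88.8% rather than 83.4%.

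**Step 4: conditional error from chance imbalance.** Given an observed baseline difference D between arms, the change-score estimate is off by −(1 − rho) × D. For an assumed D of 0.03, the size is 0.5 × 0.03 = 0.015 at rho 0.5 and 0.2 × 0.03 = 0.006 at rho 0.8. That is 21% and 9% of the 0.07 target.

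**Step 5: imbalance from recruitment.** Data were simulated with 142 clusters of 17, ICC 0.1, rho 0.5 and a 0.04 difference between arms, using least-squares point estimates. Bias in the estimated effect:

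| source of the difference | change score | baseline-adjusted |
|---|---|---|
| selection on observed baseline EQ-5D-5L | +0.021 | +0.001 |
| stable trait difference | 0.000 | −0.020 |
| shift in baseline answers only | +0.040 | +0.020 |
| worse prognosis not seen in baseline EQ-5D-5L | −0.040 | −0.040 |

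Neither method is better in every row.

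**The case against.** The strongest reply is that this is a condensed article. It lists stratification factors without saying that they are the only covariates, and a model for change that also contains baseline would fit its wording. The unseen analysis plan may include it. That stands as a caution: the article does not exclude baseline. But it does state an outcome, a model and a covariate set, and baseline is absent from that set, so asking for it to be named is fair.

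The second reply is that nothing in the plan is wrong. Outcome, sample size and model agree with each other, and the figures reproduce. That also stands.

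A reader might go further and infer that the change-score analysis is biased and that adjustment would cure it, because centres are randomised before patients are invited (section {15}), concealment ends at the site initiation visit (section {16b}) and clusters are unblinded (section {17a}). The article does not support that. Over repeated randomisation, chance imbalance causes no bias; its effect is already inside the SD of change and so inside the planned power. It must not be counted again on top of the precision loss. For imbalance due to recruitment, adjustment works only when selection acts through the observed baseline score. Under a stable difference between arms it adds a bias that the change score does not have. The article does not show which mechanism, if any, would operate.

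**Conclusion.** The point holds as a free improvement, not as an error. The planned primary analysis is valid but less efficient than it could be. Under equal SDs and a constant design effect, adjustment cuts the variance by 35% to 10% for rho 0.3 to 0.8 and adds about 3 to 8 percentage points of power at the planned size. If 2422 is the number recruited and 80% complete, it adds about 4 to 12 points, but restores the planned power only for rho up to about 0.6.

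The size of the gain rests on rho, which the article does not give. With unequal SDs the formula changes, and the gain vanishes if the regression slope of the 12-month score on baseline equals 1. The ICC may also change after adjustment. The secondary benefit is protection against the conditional error from chance imbalance in the observed baseline score. Protection against recruitment bias in general is not part of the conclusion.

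**What to change.** In section {20a}, name baseline EQ-5D-5L utility as a covariate in the primary GEE alongside the stratification factors, with clustering on the randomised unit. The outcome may stay as change or become the 12-month value; with baseline in the model the treatment estimate is the same. Use the matching baseline value for VAS, SONG-HD Fatigue and the 6-month outcomes.

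Keep the unadjusted change-score analysis as a sensitivity analysis, because the two can differ if recruitment after randomisation makes the arms differ.

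The cost is one covariate and one parameter. A change score already needs the baseline value, so no participant is lost and no new data are needed. The wording should be fixed before outcome data are analysed by arm, so that the covariate is not a post hoc choice.
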